**Methods:**

Canadian e-Platform to Promote Behavioral Self-Management in Chronic Heart Failure (CHF-CePPORT) is a multi-site, double blind, randomized controlled trial with a 2 parallel-group (e-Counseling + Usual Care vs e-Info Control + Usual Care) by 3 assessments (baseline, 4-, and 12-month) design. We will identify subjects with New York Heart Association Class II or III systolic heart failure from collaborating CHF clinics and then recruit them (n=278) by phone. Subjects will be randomized in blocks within each site (Toronto, Montreal, and Vancouver). The primary outcome will be improved quality of life, defined as an increased number of subjects with an improvement of ≥5 points on the summary score of the Kansas City Cardiomyopathy Questionnaire. We will also assess the following secondary outcomes: (1) diet habits, depression, anxiety, smoking history, stress level, and readiness for change using self-report questionnaires, (2) physical activity level, current smoking status, and vagal-heart rate modulation by physiological tests, and (3) exercise capacity, prognostic indicators of cardiovascular functioning, and medication adherence through medical chart review. The primary outcome will be analyzed using generalized estimation equations with repeated measures on an intention-to-treat basis. Secondary outcomes will be analyzed using repeated-measures linear mixed models with a random effects intercept. All significant main effects or interactions in the statistical models will be followed up with post hoc contrasts using a Bonferroni correction with a 2-sided statistical significance criterion of *P*<.05.

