#### Secondary Hypotheses

Our secondary hypotheses are that the e-Counseling + Usual Care arm will be associated with significant improvement in the quality of life, adherence to self-care, and psychological adjustment from baseline to 4- and 12-month assessments. These outcomes will be measured using the following objective and validated indices: (1) the KCCQ (≥5 points increase in the summary score at the 4-month assessment) for quality of life, (2) the Canadian version of the Diet History Questionnaire II (DHQ II) [40] for diet habits, (3) the mean 4-day step count (as measured by accelerometry) [41,42] and the Physical Activity Scale for the Elderly (PASE) questionnaire [43] for physical activity level, (4) the medication possession ratio (MPR) [20] for medication adherence, (5) the generalized anxiety disorder (GAD-7) scale [44] and Patient Health Questionnaire (PHQ-9) [45] for anxiety and depressive symptoms, respectively, (6) the Perceived Stress Scale (PSS) [46] for stress level, and (7) Prochaska’s algorithm [47] for readiness to change self-care behaviors.

In addition, we hypothesize that the e-Counseling + usual care group will perform better than the Control groups at the 12-month assessment on the following prognostic measures of cardiovascular functioning: (1) increased exercise capacity as measured by the 6-minute walk test (6MWT) [48], (2) increased vagal-heart rate modulation [44,45] as measured by electrocardiography (ECG), (3) decreased values of the Seattle Heart Failure Model (SHFM) [49-51], N-terminal pro-brain natriuretic peptide (NT-proBNP) [52,53], high sensitivity C-reactive protein (hsCRP) [52,54], and (4) increased VO_2_ peak [55] during cardiopulmonary exercise testing.

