Schedule for proactive e-messages	Weekly	Biweekly	Monthly
Total # of proactive e-messages	16	8	4

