#### Statistical Analysis

This trial will use a 2 parallel-group design with 3 repeated assessments at baseline, 4-, and 12-months. A generalized mixed model (GMM) will evaluate the primary outcome, which is a binary code of whether the 12-month KCCQ [39] increases ≥5 points [38]. Predictors will include baseline KCCQ, age, sex, body mass index, and Group (e-Counseling vs Control). The primary outcome will be coded as a “failure” in the event of CHF hospitalization or mortality, but not for “elective” medical procedures (eg, cardiac resynchronization therapy). GMM with repeated measures will assess binary secondary outcomes across 4- and 12-month intervals (eg, KCCQ and smoking status). This analysis is optimal as it adjusts for serial correlations across repeated measures and between individual subjects in each group. Predictors will include baseline KCCQ, age, sex, body mass index, time (4- vs 12- month assessment interval), and Group (e-Counseling vs Control). Significant interactions or main effects will be followed by Bonferroni post hoc tests for significance, *P*<.05, 2-sided. Data missing at random will be handled by multiple imputations. For continuous secondary outcomes, linear mixed models (LMM) [94] for repeated measures with a random intercept will assess whether within-subject improvement across 4- and 12-month intervals is independently associated with our e-Counseling protocol. This analysis adjusts for serial correlations across repeated measures and between subjects in each Group. Predictors will include the baseline dependent variable, age, sex, body mass index, time (4- vs 12-month assessment interval), and Group (e-Counseling vs Control). LMM with a random intercept will also evaluate whether e-Counseling vs Control demonstrates improvement at the 12-month interval in VO_2_ peak, NT-proBNP, hsCRP, and the SHFM.

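### The two-visit models for secondary outcomes list time and Group but no Group-by-Time term, so as listed they do not give the separate 4- and 12-month effects that the secondary hypotheses ask about

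*Protocol article*

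**What the plan says.** The Statistical Analysis section of the protocol article describes three kinds of model.

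- **Primary outcome.** A generalized mixed model for a single-visit response, "which is a binary code of whether the 12-month KCCQ [39] increases ≥5 points". Its terms are given as "Predictors will include baseline KCCQ, age, sex, body mass index, and Group (e-Counseling vs Control". There is no time term.
- **Binary secondary outcomes at 4 and 12 months**, with KCCQ response and smoking status as examples. A repeated-measures generalized mixed model: "Predictors will include baseline KCCQ, age, sex, body mass index, time (4- vs 12- month assessment interval), and Group (e-Counseling vs Control".
- **Continuous secondary outcomes at 4 and 12 months.** A linear mixed model with a random intercept: "Predictors will include the baseline dependent variable, age, sex, body mass index, time (4- vs 12-month assessment interval), and Group (e-Counseling vs Control".

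After the binary list, the section adds: "Significant interactions or main effects will be followed by Bonferroni post hoc tests for significance". The abstract makes a similar statement for the models in general: "All significant main effects or interactions in the statistical models will be followed up with post hoc contrasts using a Bonferroni correction". Neither place says which interaction is meant.

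The Secondary Hypotheses section asks for improvement from baseline to both follow-up visits. For quality of life it names one visit: "≥5 points increase in the summary score at the 4-month assessment". The Secondary Outcomes section repeats that 4-month endpoint.

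**The concern.** A model with time and Group as main effects assumes that the treatment effect is the same at both visits. It estimates one Group coefficient, and a contrast taken at 4 or at 12 months returns that same coefficient. The secondary hypotheses need more than this. One of them is specific to 4 months, and the trial's declared purpose is long-term adherence, which depends on whether an early gain lasts.

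The two visits also follow different contact intensities. Table 1 sets the messages at "Weekly Biweekly Monthly" over successive four-month periods, which is 16, 8 and 4 messages. An effect that differs between visits is therefore a possibility the analysis should be able to show. If KCCQ response at 4 months is read from the pooled coefficient, the result would also partly re-use the 12-month data that define the primary endpoint.

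**Working it through.** **Step 1: compare the lists with the follow-up rule.** The binary list holds baseline KCCQ, age, sex, body mass index, time and Group. The continuous list holds the baseline value of the outcome, age, sex, body mass index, time and Group. Neither contains a product term. The follow-up rule refers to interactions in the models. Time (4 vs 12 months) and Group each have two levels, so a significant main effect of either leaves no further pairwise comparison to correct. The Bonferroni step has content for these factors mainly if an interaction is fitted. The text therefore relies on a term that it does not list.

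**Step 2: which outcomes are reached.**

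- Reached: outcomes analysed at both 4 and 12 months, namely KCCQ response as a secondary outcome, smoking status, and the self-care and psychological measures.
- Not reached: the primary model as the Statistical Analysis section gives it, since it has no time term. Also not reached are VO2 peak, NT-proBNP, hsCRP, the Seattle Heart Failure Model score, the 6-minute walk test and heart rate variability, which have one post-baseline assessment at 12 months.

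**Step 3: the plan's own figures.** No stated sample-size figure depends on a two-visit model. The 93 per group for 53% vs 33% at 12 months reproduces with unpooled variances: (1.960 + 0.842)² × (0.53 × 0.47 + 0.33 × 0.67) / 0.20² = 92.3, so 93. Adding Group-by-Time does not change it.

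**Step 4: illustration of what pooling does to a continuous outcome.** The 115 per group comes from the Sample Size Estimation section. Everything else is assumed: SD of 1 at each visit, within-subject correlation ρ of 0.3 to 0.7, complete data, two-sided 5% level, normal approximation. With d4 and d12 the true effects:

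- Pooled Group effect = (d4 + d12)/2, with SE = √[(2/n)(1 + ρ)/2] = 0.106 (ρ = 0.3) to 0.122 (ρ = 0.7).
- Group contrast at one visit: SE = √(2/n) = √(2/115) = 0.132.
- Interaction (d12 − d4): SE = √[(2/n) × 2(1 − ρ)] = 0.156 (ρ = 0.3) to 0.102 (ρ = 0.7).
- Probability of significance = Φ(|d|/SE − 1.96) + Φ(−|d|/SE − 1.96).

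| d4, d12 (SD) | Pooled estimate | Pooled significant | 4-month contrast significant | 12-month contrast significant | Interaction significant |
|---|---|---|---|---|---|
| 0.5, 0 | 0.25 | 0.538–0.652 | 0.966 | 0.050 | 0.893–0.998 |
| 0.5, 0.2 | 0.35 | 0.821–0.909 | 0.966 | 0.329 | 0.485–0.836 |
| 0.3, 0.3 | 0.30 | 0.694–0.806 | 0.624 | 0.624 | 0.050 |
| 0, 0.4 | 0.20 | 0.377–0.469 | 0.050 | 0.858 | 0.727–0.975 |

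In the first row the pooled model would often be read as a benefit that no longer exists at 12 months. In the last row it would often miss a late benefit. In the third row pooling is the more powerful analysis.

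**Step 5: if the interaction is implied.** The stated rule follows up only significant terms. In the second row the effect falls by 0.3 SD, yet the interaction test reaches significance in only 48.5% to 83.6% of trials. It would not open the visit-specific comparison in the remaining 16.4% to 51.5%. A significant Group effect could also trigger follow-up, but the article does not say that this would be done by visit.

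**The case against.** The strongest reply is that the article describes predictors, not a complete model formula. It mentions interactions twice, and Group-by-Time is the natural one for this design. Exact model terms are often left to a full protocol or analysis plan, which is not shown. This has weight. A reader might infer that the models force a common effect and cannot test any time-specific hypothesis. The documents do not support that, because the authors evidently foresee interactions. What remains is that the article states the lists, leaves the interaction out of both and names it nowhere. Its Planned Subgroup Analysis section, on sex, age and income, leaves open that another interaction was meant.

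The second reply is that the pooled effect is legitimate. Baseline is a covariate rather than a repeated response, so the Group coefficient is a valid average treatment effect after baseline. It also matches the stated aim of the linear mixed model, which is improvement across the two intervals. This stands in full. The point is that the average does not answer the visit-specific questions, not that it is biased.

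The third reply is that the illustration is assumed and linear. This also stands. Simple averaging holds for balanced continuous data. In a binary model the common effect lies on the link scale, and differences in percentage points need not be equal at the two visits. A reader might also infer from Table 1 that the effect will fade. The table shows only a tapering schedule and gives no evidence on effect.

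**Conclusion.** The concern holds for the secondary outcomes analysed at both visits. As listed, their models give one average post-baseline Group effect, while the follow-up rule refers to interactions that are not specified. The 4-month KCCQ hypothesis and the separate 4- and 12-month secondary questions therefore have no direct test on the page. If the interaction is implied, follow-up is still conditional on a significant term.

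The size cannot be taken from the documents. The figures above show what could happen under assumed effects and correlations, not what is expected.

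A reader might infer that the primary result is also compromised. The Statistical Analysis section does not support this, since its primary model concerns 12 months alone. One loose end remains: the abstract describes the primary analysis as generalized estimating equations with repeated measures. If that description governed, the same gap could reach the primary outcome, so the two accounts need to be reconciled.

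This should be changed before analysis, but it does not threaten the primary comparison as the Methods specify it.

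**What to change.** - Add Group-by-Time to the repeated-measures generalized mixed model and to the two-visit linear mixed model.
- Pre-specify the Group contrast at 4 months and at 12 months from each model, with confidence intervals. Report both whether or not the interaction or a main effect is significant. The average over visits can be kept as an additional summary.
- Name the interactions to which the Bonferroni follow-up applies.
- Make the abstract and the Statistical Analysis section agree on the primary method and on whether it uses one visit or two.

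The cost is one extra term per model and no change to any stated sample size. Each visit-specific interval is wider than the pooled one by a factor of √[2/(1 + ρ)]. That is about 24% at ρ = 0.3 and 8% at ρ = 0.7 (assumed correlations, as above). If the true effect is the same at both visits, some power is given up, as the 0.3, 0.3 row of the table shows.

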#### Planned Subgroup Analysis

Subanalyses will explore whether therapeutic changes in primary or secondary outcomes following e-Counseling differ significantly within subgroups–sex, age, and income level. We will use GMM to evaluate the dose-response relationship between e-Counseling and improvement in our primary outcome; and LMM to evaluate this dose-response relationship for prognostic measures of CHF at the 12-month outcome using a ratio of adherence to treatment (number of emails sent/number of emails opened).

#### Quality Control and Quality Assurance Procedures

Three committees will be established for quality control and quality assurance purposes. The Steering Committee will hold teleconference meetings every 3 months to review trial progress, overall outcome rates, issues related to evaluation of primary or secondary outcomes, and response of research staff to any adverse incidents. This group will recommend whether our trial should continue without protocol modification, with modification, or whether it should be terminated. The Outcome Adjudication Committee will meet every 6 months by teleconference to adjudicate issues related to primary outcome status of subjects. The Safety and Monitoring Committee will meet annually with the option of expedited meetings in the event of an urgent issue or unexpected “serious adverse event.”

## Discussion

### CHF-CePPORT Benefits to CHF Patients

It is critical for preventive eHealth care in Canada to establish a foundation upon which a pan-Canadian e-platform can be built for patients with CHF in order to improve the quality of life and adherence to self-care behaviors. It is reasonable to expect that CHF-CePPORT will provide data that is indispensible in helping investigators in Canada to develop a compelling Phase 3 trial where the independent benefit of e-Counseling for CHF can be evaluated with regard to decreasing HF hospitalizations and mortality-as has been shown for telehealth [35,70,95].

### CHF-CePPORT Findings

Findings from CHF-CePPORT will also help guide the development of CHF e-Counseling services provided by the Heart and Stroke Foundation of Canada. Their Consumer eHealth platform offers visibility and accessibility for disseminating information and resources developed by CHF-CePPORT through its website. In 2011, this e-platform accommodated 395,044 users who searched for heart health information, while 160,600 users completed structured risk assessments. Second, our results will be submitted for presentation at national meetings and peer-reviewed publications. Third, the Heart and Stroke Clinical Update is an annual continuing medical education conference hosted by the Heart and Stroke Foundation of Canada for primary care physicians. Pending the results of this study, there is interest to develop a workshop for Canadian physicians and health professionals on the use of our e-platform to promote self-care in patients with CHF. As results become available, our team will develop a knowledge translation supplement grant.

### The e-Platform in CHF-CePPORT

The proposed e-platform in CHF-CePPORT is designed to complement (rather than compete with) e-programs that are housed in collaborating institutions. Following our trial, our aim is to build supplementary e-links to specialized programs in participating CHF clinics within Canada. At the same time, we expect that the e-platform in CHF-CePPORT will evolve as an e-Counseling resource for CHF clinics through collaborations with other investigators. To that end, members of our research team are affiliated with societies that are engaged in knowledge dissemination and application. These affiliations will permit direct dissemination of study outcomes to key opinion leaders and facilitate uptake of new knowledge to a broader audience.

## Abbreviations

6MWT: 6-minute walk test
BNP: brain natriuretic peptide
CHF: chronic heart failure
CHF-CePPORT: Canadian e-Platform to Promote Behavioral Self-Management in Chronic Heart Failure
COHRT: Community Outreach Heart Health and Risk Reduction Trial
CONSORT: Consolidated Standards of Reporting Trials
DHQ II: Diet History Questionnaire II
ECG: electrocardiography
GAD-7: generalized anxiety disorder
GMM: generalized mixed model
HF-ACTION: Heart Failure: A Controlled Trial Investigating Outcomes of Exercise Training
hsCRP: high sensitivity C-reactive protein
IQR: interquartile range
I-START: Internet-Based Strategic Transdisciplinary Approach to Risk Reduction and Treatment
KCCQ: Kansas City Cardiomyopathy Questionnaire
LMM: linear mixed models
LVEF: left ventricular ejection fraction
MI: motivational interviewing
MPR: medication possession ratio
NT-proBNP: N-terminal pro-brain natriuretic peptide
NYHA: New York Heart Association
PASE: Physical Activity Scale for the Elderly
PHQ-9: Patient Health Questionnaire
PSS: Perceived Stress Scale
REACH: Promotes Blood Pressure Reduction and Therapeutic Lifestyle Change in Hypertension
RR: relative risk
SHFM: Seattle Heart Failure Model
UHN: University Health Network
